#### Pittsburgh Sleep Quality Index questionnaire (PSQI)

Given that actigraphy distinguishes wakefulness from sleep based on movements and that there is a possibility that a person with poor sleep quality may stay awake while lying still, the Pittsburgh Sleep Quality Index questionnaire will be used. The PSQI is the most commonly used measure for subjective self-report sleep quality. In a study that examined test-retest reliability in a sample of 76 individuals with insomnia over a period of 2 days to several weeks, the PSQI showed a correlation of 0.87 for global score (34). This 24-item questionnaire captures “overall” subjective sleep quality and will be used before and after each intervention. This instrument gives an accumulative score based on seven subcomponents: subjective sleep quality, sleep latency, sleep duration, habitual sleep efficiency, sleep disturbances, use of sleeping medication, and daytime dysfunction (35). The total score ranges from 0 (good sleep quality) to 21 (poor sleep quality) with a 0–3 scoring range for each of the seven subcomponents (35). To assess significance, baseline scores will be compared to music alone, BBFs alone, and music with BBF.

#### Philips Actiwatch Spectrum Pro actigraphy monitor

Since this study will not be conducted within a sleep laboratory using polysomnography, the Philips Actiwatch Spectrum Pro monitor will be used for home use. This clinical grade tri-axial accelerometer-based wearable device works by measuring movement of the body. Using special software, that information is then articulated into a graphical and tabulated report that shows the movement that occurred throughout the wake and sleep cycles. The report gives the: (1) time the participant went to bed, (2) time awaken, (3) number of hours in bed, (4) total number of hours asleep, (5) number of minutes it took to fall asleep, (6) sleep efficiency percentage, (7) number of minutes awaken after sleep onset, and (8) total number of times awaken after falling asleep. Measures will be collected during all phases. All phases will be analyzed to assess the trends and any statistical differences across time. The device also measures level and type of light exposure in the event the investigator wants to assess if light exposure played a role in the analysis given that some of the participants may work varying shifts (e.g., sleeping at night vs. sleeping during the day) (36). In a 2020 systematic review assessing the utility of sleep actigraphy, the Actiwatch was one of the most used devices with one third of the 34 studies reviewed reporting high participant compliance and low rate of device malfunction (4–6.7%) (37).

#### National Sleep Foundation sleep diary (version 6)

The National Sleep Foundation Sleep Diary is a short 15-item questionnaire that captures the daily habits that may influence sleep. The questionnaire is divided into two parts, seven questions to be completed upon awakening and eight questions to be completed at bedtime. Given that most of the questions upon awakening will be captured by the actigraphy monitor, these questions will not be utilized for the study. As for the questions to be completed at bedtime, these address: (1) exercise, (2) medication use, (3) napping, (4) sleepiness during the day, (5) mood, (6) alcohol, food and caffeine intake, (7) timing of caffeine intake, and (8) bedtime routine. This instrument is not scored but will be used to assess patterns and if those patterns affected the sleep outcomes (38). According to the literature, it is recommended that persons wearing actigraphy monitors also use a sleep diary as it captures subjective data that an actigraphy monitor cannot detect (39).

#### Post-study questionnaire

The Post-Study Questionnaire is a 10-item multiple choice and open-ended questionnaire designed by the investigator to capture subjective data regarding the participant's experience and perception of BBFs. This data will be used to improve the rigor and participant reliability for Phases 3 and 4. Questions include: (1) one word description of their experience, (2) perception if they were able to distinguish if they were receiving BBFs (applies to Cohort 2 only), (3) adherence to the protocol, (4) factors that affected adherence, (5) ease of use of the equipment, (6) level of comfort while using the equipment, (7) willingness to explore other uses for BBFs, (8) willingness to recommend BBFs to colleagues, friends, and family, (9) willingness to participate in a future BBF study in the confines of a sleep lab, and (10) comments or recommendations to the investigator.

### Power analysis and data analysis plan

For Cohort 1, since the study is comparing three measures, a 2 × 3 mixed ANOVA (between and within subject factor) will be used. The parameters for this analysis were as follows: (1) power of 1—β = 0.85, (2) level of significance of α = 0.05, (3) an autocorrelation parameter (i.e., average correlation) ranging from 0.3 to 0.7 (in increments of 0.2), and (4) a standardized effect size (F) ranging from small (0.1) to medium (0.25) in 0.05 increments. Using GPower software, the sample size estimates range from *n* = 52 (when the correlation of the repeated measures = 0.7 and the standardized effect size is *F* = 0.25) to *n* = 116 (when the correlation of the repeated measures = 0.3 and the standardized effect size is *F* = 0.1). For this study a sample of 106 will be sufficient (84 required, plus 25% for attrition bringing the total to 105 and the addition of 1 to make both arms equal in number).

For Cohort 2, assuming there is no difference in mean sleep efficiency score (i.e., mean difference = 0) between the interventions (BBF only, music with BBF) a sample size of 61 participants (plus 1 to make group equal in number *n* = 62) would be needed to declare with at least 80% power that the intervention effect in BBF only is the same as in music with BBF. Given that Cohort 1 is *n* = 106 and that propensity score matching with replacement will be implemented to make the groups comparable, the final test for intervention effect will be carried out with a power in excess of 80%.

For this two-period 2-arm cross-over design where each subject gets both treatments and repeated outcome measurements over time, a linear mixed model with repeated measures (MMRM) approach will be used. Unless otherwise stated, all statistical tests will be 2-sided with the probability of a Type I error not to exceed 0.05. Descriptive statistics will be used for all quantitative and qualitative variables at all data collection points. Continuous variables will be tabulated using N, mean, standard deviation or standard error (as appropriate), median, minimum, and maximum values. For categorical variables, frequency counts and percentages will be presented.

Actual values and change from baseline in the different Sleep Actigraphy report outcome variables will be summarized by time point and sequence group using descriptive statistics. Analysis will be conducted for the following variables: number of hours in bed, total number of hours asleep, number of minutes it took to fall asleep, percent efficiency of sleep, number of minutes awaken after sleep onset, and total number of times awaken after falling asleep. Sleep efficiency will be used as the main indicator for improvement of sleep quality and will be calculated by dividing the amount of time spent asleep (in minutes) by the total amount of time in bed (in minutes) and multiplying it by 100. Study parameters include sleep latency <30 min, wakefulness after sleep onset <30 min, decreased frequency in number of awakenings, total sleep time >6 h and sleep efficiency >80%.

Qualitative measures of sleep obtained from the PSQI will be analyzed using descriptive statistics. As for the National Sleep Foundation Sleep Diary entries, summary statistics will be provided at the different data collection time points. To further improve the precision of the estimates, items from the National Sleep Foundation Sleep Diary scores and light exposure (sleeping at night vs. sleeping during the day) may be entered into the model as additional covariates. To assess if the participants' personal characteristics' affect the outcome a two-step modeling approach will be followed. First, the effect of each demographic variable will be evaluated separately in a series of separate MMRM models that include each study outcome as the dependent variable and the demographic characteristic and time as predictors. All demographic factors will then subsequently be entered into a MMRM model that also incorporate intervention, period, sequence as fixed effects, and study participant as a random effect.

For the match group analysis between Cohorts 1 and 2, propensity score matching will be implemented to construct a sample of subjects which have similar baseline covariate distributions between the cohorts. A logistic regression model, with intervention cohort as the dependent variable, will be employed to estimate the conditional distribution of the intervention given the covariates. The predictors in this model are baseline characteristics believed to be related to the main study outcome of interest (e.g., sleep efficiency score). To make optimal use of the number of subjects enrolled in Cohort 1, a match and replace method will be used whereby a BBF embedded with music user could be matched to more than one BBF only user. This will help maximize the number of matched BBF participants while enhancing the ability of the study to detect a difference in intervention between the two cohorts if indeed there is one.

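### Both ends of the Cohort 1 sample-size range carry the wrong effect size: 52, 84 and 116 are all F = 0.15 results, so the text implies more sensitivity to small effects than the design has

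*Protocol article*

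**What the plan says.** All of this is in the Protocol article, Power analysis and data analysis plan, first paragraph.

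- **Design:** "since the study is comparing three measures, a 2 × 3 mixed ANOVA (between and within subject factor) will be used".
- **Error rates:** "power of 1—β = 0.85" and "level of significance of α = 0.05".
- **Correlation:** "an autocorrelation parameter (i.e., average correlation) ranging from 0.3 to 0.7 (in increments of 0.2", that is 0.3, 0.5 and 0.7.
- **Effect size:** "a standardized effect size (F) ranging from small (0.1) to medium (0.25) in 0.05 increments", that is 0.10, 0.15, 0.20 and 0.25.
- **Lower end of the G*Power range:** "n* = 52 (when the correlation of the repeated measures = 0.7 and the standardized effect size is *F* = 0.25".
- **Upper end:** "n* = 116 (when the correlation of the repeated measures = 0.3 and the standardized effect size is *F* = 0.1".
- **Conclusion:** "For this study a sample of 106 will be sufficient". This is built from 84 evaluable participants, a 25% addition for attrition (84 × 1.25 = 105), and one more to equalise the arms.

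The paragraph does not say which effect size and correlation the 84 belongs to. It never names F = 0.15 as the design effect.

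**The concern.** The two endpoints are too close together for their labels. In this test the required n scales roughly with (1 − rho)/F². From (rho 0.7, F 0.25) to (rho 0.3, F 0.1) that quantity goes from 0.3/0.0625 = 4.8 to 0.7/0.01 = 70, a rise of about 14.6-fold. The printed rise is 116/52 = 2.2-fold, which is close to what the correlation alone would produce at a single effect size (0.7/0.3 = 2.3).

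This paragraph is the only justification given for the size of Cohort 1. A reader told that 116 is the most demanding case on a grid reaching down to F = 0.1, and that 106 suffices, will take the trial to be more sensitive to small effects than it is. With the basis for the 84 unstated, the two endpoints are all that the reader has to judge by.

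**Working it through.** **Inputs.** From the power paragraph: k = 2 groups, m = 3 measures, alpha 0.05, power 0.85, rho 0.3/0.5/0.7, F 0.10 to 0.25 in steps of 0.05, G*Power. Not stated: the nonsphericity correction epsilon, assumed to be 1. N is the total, rounded up to an even number for two equal groups.

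**Formula** (within-subject factor and group-by-time interaction; the two coincide for k = 2):

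- lambda = F² · N · m / (1 − rho)
- df1 = (k − 1)(m − 1) = 2; df2 = (N − k)(m − 1) = 2(N − 2)
- power = P(noncentral F with df1, df2, lambda exceeds the central 95% point)

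**The two printed settings.**

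- rho 0.7, F 0.25: N = 20 gives lambda = 0.0625 × 20 × 3 / 0.3 = 12.5 on (2, 36) df and power 0.868; N = 18 gives 0.825. The requirement is 20. The printed 52 would give power above 0.999.
- rho 0.3, F 0.1: N = 116 gives lambda = 0.01 × 116 × 3 / 0.7 = 4.97 on (2, 228) df and power 0.496. N = 258 gives lambda = 11.06 and power 0.852; N = 256 gives 0.849. The requirement is 258.

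**Where the printed numbers come from.** Smallest even N for 85% power:

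| F | rho 0.3 | rho 0.5 | rho 0.7 |
|---|---|---|---|
| 0.10 | 258 | 184 | 112 |
| 0.15 | **116** | **84** | **52** |
| 0.20 | 66 | 48 | 30 |
| 0.25 | 44 | 32 | 20 |

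All three numbers in the paragraph, including the unexplained 84, are the F = 0.15 row. At that effect size lambda is 11.19, 11.34 and 11.70, with power 0.854, 0.857 and 0.864. The range over the stated grid is 20 to 258.

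**Alternatives tried.** The between-subjects test (lambda = F² · N · m / (1 + (m − 1)rho)) gives 482/602/722 at F 0.10 and 80/98/118 at F 0.25. Epsilon of 0.9, 0.75 and 0.5 gives 22, 24 and 32 at the setting labelled 52, and 278, 316 and 422 at the setting labelled 116. Other effect-size conventions, numbers of groups or measures, power levels and alphas were also tried. None reproduces both printed endpoints.

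**Power at F = 0.1.**

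| N | rho 0.3 | rho 0.5 | rho 0.7 |
|---|---|---|---|
| 84 | 0.37 | 0.50 | 0.73 |
| 106 | 0.46 | 0.60 | 0.83 |
| 116 | 0.50 | 0.65 | 0.87 |

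**What 84 completers can detect.** 85% power is reached at F of about 0.176, 0.149 and 0.115 for rho 0.3, 0.5 and 0.7.

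**The case against.** The number that drives enrolment is not wrong. A requirement of 84 is a correct G*Power result at a reasonable interior point of the stated grid, so the error lies in the labels and in an unstated design point, not in the sample size.

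Nor does the paragraph say that 84 or 106 has 85% power at F = 0.1. On its own printed figures, 84 falls short of the 116 quoted for F = 0.1 with rho 0.3, so a careful reader would not take that corner as covered. The article calls this a feasibility study, and nothing in it says a null result will be read as ruling out small effects. The planned analysis is a mixed model for repeated measures, so ANOVA power figures describe the sample-size calculation and not exactly the test to be run.

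All of this stands, and it limits the consequence. It does not rescue the labels. The text attaches a specific n to a specific F and correlation, and both attachments are wrong. Presenting 116 as the top of a grid reaching F = 0.1, when 258 is the requirement, still misstates sensitivity by implication.

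**Conclusion.** Both endpoint labels are wrong: 52 should be 20 and 116 should be 258 at the settings named, and the printed trio belongs to F = 0.15. The stated 85% power at F = 0.1, rho 0.3 with n = 116 is in fact 50%. Even with no attrition, 106 does not reach 85% at F = 0.1 for any listed correlation. The conclusion rests on the stated inputs and on epsilon = 1. The exact three-way match supports that value, and the smaller values tried raise the requirements without reconciling the labels.

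Three stronger readings are tempting and are not supported:

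- **That the plan claims 85% power for F = 0.1.** It implies sensitivity through the range and the word sufficient, but makes no such statement.
- **That 84 completers are adequate only when F is at least 0.15 and rho at least 0.5.** Neither condition is necessary. At F = 0.20 with rho 0.3 power is 0.93, and at rho 0.7 an F of about 0.115 is enough.
- **That the sponsor designed for F = 0.15 and rho 0.5.** The match is exact, but no passage says so.

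The paragraph needs correcting. The sample size does not follow from the mislabelled endpoints and need not change because of them.

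**What to change.** In the Cohort 1 power paragraph:

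1. Replace the range with the correct grid (the four-row table above, 20 to 258), or keep 52 and 116 and label both as F = 0.15, at correlations 0.7 and 0.3.
2. State the effect size and correlation behind the 84. It matches F = 0.15 with correlation 0.5; the sponsor should confirm this from the G*Power output before it is written as the design assumption.
3. State the nonsphericity assumption used.
4. Add the power at F = 0.1 with 84 completers (37%, 50% and 73% for correlations 0.3, 0.5 and 0.7), described as based on the mixed ANOVA.

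The cost is the rewording of one paragraph and a less favourable statement of sensitivity. Enrolment, endpoint and analysis model are unaffected.

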**Methods:**

This protocol uses a two cohort unblinded and double-blinded, randomized, pre- and post-intervention methods and crossover matched group design. In Cohort 1, a sample of 106 participants with poor sleep quality will be randomized into two groups. All participants will start with 1 week of no intervention. Group 1 will use theta/delta BBF for 2 weeks followed by 1 week of no intervention followed by music for 2 weeks. Group 2 will do the reverse. In Cohort 2, 62 participants will be blinded and randomized into two groups. Group 3 will use music for 2 weeks followed by a 1-week break followed by music embedded with theta/delta BBF for 2 weeks. Group 4 will do the reverse. Using Cohort 1 music only as a control, data will be collected using sleep actigraphy, sleep quality questionnaires, and sleep diaries with a crossover and match group analysis between cohorts to compare the effect of no intervention vs. music vs. BBF only vs. music with BBF on sleep quality.

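### Cohort 1 attrition allowance is taken on the 84 required, not on those enrolled, so 106 covers a loss of about 20.8%, not 25% (minor)

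*Protocol article*

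**What the plan says.** In the protocol article, *Power analysis and data analysis plan*, Cohort 1 is sized for a mixed ANOVA with two groups and three measures, with "power of 1—β = 0.85" and "level of significance of α = 0.05". Effect size and correlation are given as ranges: F from 0.1 to 0.25 in steps of 0.05, and correlation 0.3, 0.5 or 0.7. The section does not say which pair lies behind the chosen number.

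It then concludes: "For this study a sample of 106 will be sufficient", and justifies this in brackets: "84 required, plus 25% for attrition bringing the total to 105 and the addition of 1 to make both arms equal in number". No other attrition figure is given for this cohort. The abstract carries the same total: "In Cohort 1, a sample of 106 participants with poor sleep quality will be randomized into two groups". The Cohort 1 heading under *Study design* also gives 106.

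**The concern.** A reader who sees 25% attached to attrition will take it that the trial can lose a quarter of its Cohort 1 participants and still analyse the 84 it calls required. The printed arithmetic does not give that. It adds a quarter of the smaller number (those needed at the end), whereas dropout removes a fraction of the larger number (those who start). The two calculations agree only when attrition is zero.

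At stake is whether 106 is enough on the plan's own terms: whether the stated allowance protects the 85% power target, and what loss the trial can in fact absorb.

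**Working it through.** **Inputs, all from *Power analysis and data analysis plan*:** required N = 84; attrition figure = 25%; one added for equal arms; enrolled N = 106; power 0.85; α = 0.05; two groups, three measures.

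**1. Reproduce the plan's figure.**
84 × (1 + 0.25) = 105, and 105 + 1 = 106. The match is exact, so the allowance was applied by multiplying.

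**2. Enrolment needed if 25% of those enrolled are lost.**
N enrolled = N required / (1 − loss) = 84 / 0.75 = 112, or 56 per arm. This is 112 − 106 = 6 more than planned.

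**3. What 106 leaves after a 25% loss.**
106 × 0.75 = 79.5, so 79 or 80 completers. Shortfall: 84 − 80 = 4 or 84 − 79 = 5.

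**4. What loss 106 does cover.**
106 − 84 = 22, and 22/106 = 20.8%. Before the extra participant, 105 covers 21/105 = 20.0%.

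**5. Effect on power.** The pair of F and correlation (ρ) behind 84 is not stated, so it has to be inferred. For the repeated-measures F test (within factor, or group-by-measure interaction, which has the same degrees of freedom with two groups), the noncentrality is λ = F² × N × 3 / (1 − ρ), with 2 and 2(N − 2) degrees of freedom. I searched the plan's grid for the smallest even N reaching 0.85. Only F = 0.15 with ρ = 0.5 returns 84, and the between-group test returns 84 nowhere on the grid.

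| Completers | λ = 0.15² × N × 3 / 0.5 | df | Power |
|---|---|---|---|
| 84 | 11.34 | 2, 164 | 85.7% |
| 80 | 10.80 | 2, 156 | 83.8% |
| 79 | 10.665 | 2, 154 | 83.3% |

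Power therefore drops by 85.7 − 83.8 = 1.9 to 85.7 − 83.3 = 2.4 percentage points, and ends 1.2 to 1.7 points below the 85% target.

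A caution for anyone repeating this: the same formula does not return the section's range ends, 52 and 116, at the effect sizes printed beside them. It returns both at F = 0.15, with the printed correlations of 0.7 and 0.3. That is a separate matter, but it fits 84 having been computed at F = 0.15.

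**The case against.** **The wording may describe a top-up, not a loss rate.** The text reads "plus 25% for attrition bringing the total to 105". Taken literally, that adds a quarter to the required number, and the sum is then correct. A reader might infer that the plan states an expected 25% dropout and then fails to meet it, but the documents do not go that far, because no expected loss rate is given. This part of the objection stands, and the point is therefore put conditionally. It does not clear the sentence: no 20% rate is stated either, 25% is the only number tied to attrition, and the reader is not told what loss the enrolment covers.

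**Completers are not the whole analysis set.** The same section plans a linear mixed model with repeated measures, and *Weeks 3 and 4—Intervention 1* says that data collected before a monitor failure will be kept. Someone lost after the first intervention can still contribute baseline and first-period data. This stands as a mitigation, so the power figures above are a worst case. It does not remove the loss, because a within-person comparison of the two audio treatments needs both periods. The plan also set its own target as 84 and added an allowance for losses on that basis.

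**The power figures rest on inferred inputs.** This also stands. F = 0.15 and ρ = 0.5 are solved back from 84. At other grid points the shortfall hardly matters: with 79 completers, power is 97.0% at F = 0.15 and ρ = 0.7.

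**Conclusion.** The point holds in a limited form and is minor. The step from 84 to 105 takes the allowance on the wrong base if 25% is the loss to be tolerated. On that reading, 106 is 6 short in enrolment and leaves 4 to 5 too few completers. On any reading, 106 retains 84 only up to a loss of about 20.8%. The head-count arithmetic uses only the plan's own numbers.

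The power consequence, 85.7% down to about 83–84%, assumes a full 25% loss, complete cases only, and the inferred F = 0.15 and ρ = 0.5.

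A reader might go further and infer that Cohort 1 is materially underpowered because of this step. The documents do not support that. The step costs about 2 percentage points in the worst case. Any larger deficit at a lower correlation would come from the correlation itself and would be present with all 84 completers. Nothing here affects the design, the type I error or the estimated effect.

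**What to change.** Replace the bracketed justification in *Power analysis and data analysis plan* with a statement of the loss that 106 covers, for example:

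> 106 enrolled provides 84 completers if attrition is at most 20.8%; at 25% attrition 79–80 complete and power is about 83–84% (F = 0.15, ρ = 0.5).

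The author should confirm that F = 0.15 and ρ = 0.5 are the values behind 84, or put in the actual ones. The text should not claim that 106 covers a 25% loss; a protocol that wants to make that claim would have to quote 112.

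The cost is one sentence. Enrolment stays at 106, so the abstract and *Study design* need no change. The only price is a slightly less favourable statement of tolerated attrition or power.

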## Aims

The primary aim of this study is to assess if an audio program that has theta and delta BBFs arranged in an order that mimics a healthy adult hypnogram will improve sleep quality as evidence by an increase in sleep efficiency score when compared to a control group and no intervention. The author hypothesizes that when similar participants are matched and compared, those using BBF will have similar outcomes.

Based on the findings of the primary aim, the secondary aim of this study is to map out a plan for a series of future feasibility studies to support the development of a customizable all-night audio program to induce sleep, sustain sleep and provide a structure waking for persons with poor sleep quality (Figure 3).

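### Cohort 2 is sized to declare BBF only and music with BBF the same, but the only testing described is for a difference and no equivalence margin is given

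*Protocol article*

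**What the plan says.** In the protocol article, the Aims section gives the hypothesis for the matched comparison: "those using BBF will have similar outcomes". Similar is not given a number.

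Power analysis and data analysis plan sizes Cohort 2 "assuming there is no difference in mean sleep efficiency score (i.e., mean difference = 0) between the interventions (BBF only, music with BBF"). It arrives at "a sample size of 61 participants (plus 1 to make group equal in number", giving 62), and this number is needed "to declare with at least 80% power that the intervention effect in BBF only is the same as in music with BBF". After matching to Cohort 1 (n = 106), it adds that "the final test for intervention effect will be carried out with a power in excess of 80" percent.

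The same section sets the general rule: "Unless otherwise stated, all statistical tests will be 2-sided with the probability of a Type I error not to exceed 0.05". Nothing different is stated for the comparison between cohorts. Its paragraph on propensity score matching says that matching with replacement improves the ability of the study "to detect a difference in intervention between the two cohorts if indeed there is one".

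The article states no equivalence margin, no SD for sleep efficiency, and no rule based on a confidence interval.

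**The concern.** The hypothesis and the sample size point towards showing sameness. The testing rule and the matching paragraph point towards finding a difference. These objectives need different tests, and the power of one says nothing about the other.

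If the text is followed literally, the only outcome of the described test that could be taken as support for sameness is failure to reject. That criterion rewards imprecision: the fewer and noisier the matched pairs, the more often the hypothesis appears to be confirmed. What is at stake is the one hypothesis the article states for the comparison between cohorts, together with the power claimed for it.

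**Working it through.** **Inputs.** From Power analysis and data analysis plan: assumed difference 0, power at least 80%, two-sided alpha 0.05, Cohort 2 of 61 rounded to 62, Cohort 1 of 106 (84 required, 105 after the attrition allowance, plus 1). Margin and SD are not given, so results are in SD units. The figures treat the cohorts as independent and unadjusted.

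**1. Can the 61 be reproduced?** No. For a two-sided difference test at a true difference of 0:

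P(reject) = 2 × Φ(−1.96) = 0.05, for every N.

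So no sample size gives 80% power under the test described. A finite N at difference 0 makes sense only for an equivalence test, which needs a margin.

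**2. What margin would the sample support?** For two one-sided tests (TOST) at 5% per side and true difference 0:

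power = 2 × Φ(margin/SE − 1.645) − 1

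Setting this to 0.80 gives margin/SE = 1.645 + 1.282 = 2.926 (unrounded sum), with SE = √(1/n1 + 1/n2) in SD units.

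| Comparison | SE | Margin for 80% power |
|---|---|---|
| 62 vs 106 | 0.160 | 0.47 SD |
| 61 vs 61 | 0.181 | 0.53 SD |
| 49 vs 84 | 0.180 | 0.53 SD |

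The last row is an assumption. Going from 84 to 105 implies a loss of 1 − 84/105 = 20%. The article states no attrition for Cohort 2, and the row applies the same 20% there (62 × 0.8 = 49.6, taken as 49).

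Other readings of 61 imply other margins: 0.75 SD if 61 is the total over two groups, and 0.375 SD of the paired difference if it is a number of pairs. For assumed SDs of 5 to 12 sleep-efficiency points, 0.53 SD is about 2.6 to 6.4 points.

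**3. How often would a real difference be non-significant?**

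P(non-significant) = Φ(1.96 − d/SE) − Φ(−1.96 − d/SE)

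For 62 vs 106:
- d = 0.20 SD: d/SE = 1.25, so Φ(0.71) − Φ(−3.21) ≈ 0.76.
- d = 0.31 SD: d/SE = 1.94, so Φ(0.02) − Φ(−3.90) ≈ 0.51.

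**4. Which way do the simplifications push?** Baseline adjustment narrows the margin. With a correlation of 0.7, the top of the range used for Cohort 1, the factor is √(1 − 0.49) = 0.714, and 0.468 × 0.714 = 0.33 SD for 62 vs 106. Re-use of matched participants lowers the effective sample size and widens the margin.

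**The case against.** The strongest reply is that 61 at a difference of 0 can hardly come from anything but an equivalence calculation. A margin and an SD were therefore probably used and may stand in the full protocol or SAP, which is not shown. The two-sided rule is a default that allows exceptions. The wording about detecting a difference describes a benefit of matching with replacement, and no outcome test is named for the matched comparison. Much of this stands: the 61 cannot be called wrong, and an unprinted margin alone would not be a finding. It does not remove the conflict inside the article, where a power claim for sameness sits beside a rule and a rationale for difference testing, with no exception stated.

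Two stronger readings are tempting, and the documents do not support them.

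- A reader might infer that a non-significant result will be reported as equivalence. No section says so. It is only that no other route to sameness is described.
- A reader might infer that the supportable margin exceeds the whole effect Cohort 1 is built to detect. An effect size of F = 0.15 would correspond to 0.32 to 0.37 SD between the extreme conditions, but the article gives a range of 0.1 to 0.25 and does not tie its 84 to any one value. With the baseline adjustment shown above, the margin of 0.33 SD falls inside that interval.

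It is also fair that the comparisons of BBF with music and with no intervention rest on within-person crossover data and do not need the sameness claim.

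**Conclusion.** The point holds as a mismatch between objective and analysis. The stated power has no meaning for the difference test described, and without a margin the sameness claim has no decision rule.

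For independent, unadjusted groups of 62 and 106, a true difference of 0.20 SD would be non-significant about three times in four, and 0.31 SD about half the time. An equivalence test would have 80% power only for margins of about 0.47 SD or wider, or about 0.53 SD for 61 vs 61 or 49 vs 84. These are illustrations: adjustment and re-used matches move them in opposite directions, and no value in sleep-efficiency points can be fixed without the SD.

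This should be fixed before the matched analysis. It does not threaten the within-cohort contrasts.

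**What to change.** Choose one of two routes.

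(a) Keep the equivalence objective. State and justify a margin in sleep-efficiency points, with the assumed SD. Test by two one-sided tests, so that equivalence is declared only if the 90% CI lies inside the margin. Use a variance that allows for matching with replacement, and restate the power for that margin and the expected matched sample.

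(b) Remove the claim of declaring the effects the same, and the power attached to it. Report the between-cohort difference with a 95% CI, and state that a non-significant result will not be read as similarity.

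Route (b) is the right one if the clinically justified margin is smaller than the available sample can power. Either way, the hypothesis in Aims, the Cohort 2 sizing paragraph and the matching paragraph should describe the same objective.

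The cost is a change of wording. Route (a) also needs one power calculation and may show lower power than stated; route (b) softens the claim. Neither needs more participants or data unless the sponsor keeps equivalence with a margin narrower than the sample supports.
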